### Outcomes{12}

Quantitative outcome measures will be assessed at three distinct time points: baseline (v0), post-intervention (v6) at 6 weeks, and at follow-up, which occurs 3 months from baseline (v12).

The primary outcome measures will include assessments of cognition using Brief Assessment of Cognition in Schizophrenia (BACS) [17] and Subjective Scale to Investigate Cognition in Schizophrenia (SSTICS Tamil version) [18] and functioning using Socio-Occupational Functioning Scale (SOFS) [19], at 6 weeks.

Secondary outcome measures will include assessments of quality of life using the Manchester Short Assessment of Quality of Life (MANSA) [20] and self-esteem using Rosenberg Self-Esteem Scale (RSES) [21].

All the measures will be repeated at 12 weeks to assess if the treatment effects are sustained.

The sociodemographic details of the participants will be collected at baseline and summarized as means and proportions. The primary and secondary outcome measures will be presented using mean and standard deviation, and comparisons will be made between the treatment and control arm at 6 weeks and 12 weeks. A subgroup of 20 participants, randomly selected from the intervention group, will be asked to participate in qualitative interviews at the conclusion of the 6-week intervention. These interviews aim to explore participants’ experiences with the intervention, including identifying facilitators and barriers, suggesting adaptations, and assessing the practical delivery of the intervention.

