**Methods:**

The proposed study will be a multicenter assessor-blinded randomized controlled trial at two clinical sites in Chennai, India. The preparatory phase of the study would include translation of the manual to the local language, recruitment and training of research assistants, and pilot testing using the translated manual. The second phase will be the main randomized controlled trial (RCT), during which a total of 160 persons diagnosed with schizophrenia will be recruited from both sites. After obtaining informed consent, baseline assessments will be conducted on cognition, functioning, self-esteem, and quality of life. Participants will be randomly assigned to either the virtual CCT group or the control group using a computer-generated randomization table. End-line assessments will be conducted 6 weeks after the baseline by research assistants who are blinded to the randomization post-intervention.

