### Sample size {14}

A Sample size of 104 participants (52 in each arm) is required based on the outcome indicators of cognitive performance with an effect size of 0.64 between the intervention and control groups, with 90% power and 5% alpha error using R 4.0.3 “pwr.t.test” software. A dropout rate of 50% has been assumed based on previous experiences and studies done using CCT. Therefore, the total number of recruited subjects at both sites will be 156 rounded up to 160 participants in total [22].

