*Brief Assessment of Cognition in Schizophrenia (BACS)*: BACS includes tests of verbal memory (Verbal Memory Task), verbal working memory (Digit Sequencing Task), motor/speed (Token Motor Task), verbal fluency (Verbal Fluency Task), attention/information processing (Symbol Coding Task), and executive function (Tower of London Task). BACS scores will be converted to z-scores to provide a standard metric for combining test scores into domains and comparing performance over time, relative to healthy persons [17].*Socio-Occupational Functioning Scale (SOFS)*: SOFS is a brief and comprehensive scale that has been validated in India. It consists of 14 items to measure the social functioning of patients with schizophrenia across three domains, namely adaptive living skills, social appropriateness, and interpersonal skills. The items are scored on a 5-point scale, where “1” indicates no impairment, and “5” indicates extreme impairment. The ratings may be provided by mental health professionals, family members, or other care providers familiar with the patient. SOFS demonstrates good internal consistency (*α* = 0.91) and test–retest reliability, with intraclass coefficient of 0.95. It is reported to have satisfactory content validity, with several other types of validities established, including concurrent validity, criterion validity, discriminant validity, and construct validity [19].*Socio-demographics Questionnaire*: a questionnaire to collect socio-demographic information from all participants at baseline.*Subjective Scale to Investigate Cognition in Schizophrenia (SSTICS Tamil version)*: SSTICS is a self-report measure that is brief, with 21 items to assess complaints about memory, attention, praxia, and executive function in persons with schizophrenia. It demonstrates good internal consistency (*α* = 0.86) and test–retest reliability (rs = 0.82). The scale takes approximately 6 min to complete [18].

Secondary outcome measures include:

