## Statistical methods

### Statistical methods for primary and secondary outcomes {20a}

Statistical Package for Social Sciences (SPSS) Version 21.0 will be used to analyze the data. Descriptive statistics will be used to present sociodemographic information, continuous variables will be characterized using measures of central tendency and variability, and nominal and ordinal data will be presented as proportions (frequency). The statistical tests for inferential analysis will be chosen based on discovered distributions (parametric or non-parametric), which will be assessed using probability functions and normality tests on histograms. The effectiveness of V-CCT will be evaluated using an intention-to-treat (ITT) analysis. The mean, standard deviations, and interquartile range for each of the three time points—baseline, 6 weeks, and 12 weeks—will be computed. The significance of the variations in the means (or other parameters) of the measured outcomes will be tested by the analysis.

The primary outcomes will be the BACS scores on various domains of cognition and functioning as assessed using SOFS. Self-esteem and quality of life are the secondary outcome measures. The effect size and 95% CI will be calculated to establish the superiority of the intervention arm over the control arm. Additionally, qualitative data obtained from the semi structured interview will be coded and analyzed.

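### The primary test is to be chosen after the outcome distributions are seen, and no baseline-adjusted analysis is specified although every outcome is measured at baseline

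*Protocol article*

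**What the plan says.** Under Outcomes {12}, the primary and secondary measures are presented as means and standard deviations, and "comparisons will be made between the treatment and control arm at 6 weeks and 12 weeks".

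Under Statistical methods for primary and secondary outcomes {20a}, "The statistical tests for inferential analysis will be chosen based on discovered distributions (parametric or non-parametric"; normality is to be checked first. The same section continues: "The significance of the variations in the means (or other parameters) of the measured outcomes will be tested by the analysis". It names the BACS domains and SOFS as primary outcomes and promises an effect size with a 95% confidence interval to show superiority. The section on missing data {20c} commits to intention to treat, multiple imputation and sensitivity analyses.

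The abstract states that "baseline assessments will be conducted on cognition, functioning, self-esteem, and quality of life", and the participant timeline confirms this for every scale. The only use of those baseline scores named in the analysis section is descriptive: summaries at "baseline, 6 weeks, and 12 weeks—will be computed".

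The sample size {14} is based on a two-sample t-test "with an effect size of 0.64 between the intervention and control groups", "with 90% power and 5% alpha error using R 4.0.3". This gives 104 participants (52 per arm), increased to 156 and rounded to 160 for an assumed 50% dropout.

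**The concern.** Two features of the analysis section matter here.

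**The test depends on the data.** A parametric test compares means, while a rank test compares the ordering of two distributions. Choosing between them once the distributions are known leaves the primary estimand open until the outcome data exist. Different BACS domains and SOFS could end up answering different questions, and the person making the choice has discretion. The promised effect size and interval are undefined until the test is chosen. The choice also sits awkwardly with multiple imputation. A mean difference and its standard error pool directly, whereas a rank-test p-value does not, and a normality check could come out differently in different imputed data sets.

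**No baseline-adjusted analysis is specified.** The scores are collected for every outcome. Conditioning on them reduces residual variance and corrects for chance imbalance between arms. If they are used only descriptively, precision that costs nothing is left unused. That matters more in a trial that expects heavy dropout.

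**Working it through.** **Inputs from the document.** Effect size d = 0.64, power 90%, alpha 5%, 52 per arm, 1:1 allocation, 160 recruited, 50% dropout. Sidedness is not stated.

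**Assumptions.** r, the correlation between baseline and 6-week score, is not given; I use 0.3 to 0.7. I take 0.64 to be standardised on the unadjusted 6-week standard deviation, which the document does not state.

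**Step 1: reproduce the stated figure.** With the two-sided normal approximation,

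n per arm = 2(1.960 + 1.282)² / 0.64² = 21.02 / 0.4096 = 51.3, rounded up to 52, or 104 in total.

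This matches. The t-distribution version gives 52.29, hence 53 per arm, and its power at 52 per arm is 89.8%. A one-sided test would give 42 per arm and does not match. The sample size is therefore that of an unadjusted, two-sided, two-sample comparison.

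**Step 2: effect of baseline adjustment.** Adjusting for a baseline with correlation r multiplies the residual variance by 1 − r², so the effective standardised difference is

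d_adj = 0.64 / √(1 − r²).

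- r = 0.3: 0.64 / √0.91 = 0.671
- r = 0.5: 0.64 / √0.75 = 0.739
- r = 0.7: 0.64 / √0.51 = 0.896

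**Step 3: power (two-sided 5%, t-distribution).**

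| Analysed per arm | Unadjusted | r = 0.3 | r = 0.5 | r = 0.7 |
|---|---|---|---|---|
| 52 (the stated requirement) | 89.8% | 92.3% | 96.2% | 99.5% |
| 40 (160 × 0.5 / 2) | 80.7% | 84.2% | 90.4% | 97.7% |

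The second row applies only if 50% dropout means that 50% of outcomes are missing. In that case the smallest r that brings power back to 90% is about 0.49.

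**Step 4: what the document says about r.** It reports test-retest reliability for SOFS ("with intraclass coefficient of 0.95") and 0.82 for SSTICS. These make r of 0.5 or more plausible for those two scales. They are repeatability figures, though, not correlations across six weeks of intervention. No such figure is given for BACS, and the sample size rests on cognitive performance.

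**Step 5: does the choice of test matter?** In simulation with 52 per arm and d = 0.4, the t-test and the Mann-Whitney test fell on opposite sides of 5% in about 7% of normally distributed data sets. For skewed data the figure was 25% to 37%, depending on the skewed shape assumed. These shapes are illustrative and are not taken from the document. Type I error under the two-stage rule stayed near 5%.

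**The case against.** The strongest objection is that non-use of baseline is inferred from silence. The sentence under Outcomes {12} says which groups are compared and when, not by what model; an ANCOVA or mixed model is also a comparison of arms at 6 and 12 weeks. The wording on variation in means could cover a repeated-measures analysis. Covariates are commonly left to a SAP, which is not shown, and baseline may enter through the imputation model. Sizing a trial by an unadjusted t-test and then analysing with adjustment is common and conservative. **This stands.** A reader might infer that the trial will discard its baseline scores; the document supports only that no baseline-adjusted analysis is specified.

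A reader might also infer that the lack of adjustment leaves the trial underpowered. That does not follow. At 104 analysed, unadjusted power is already about 90%. The 81% arises at 80 analysed, because the dropout allowance multiplies 104 by 1.5 (156) instead of dividing it by 0.5 (208), which is a separate error. Participants who drop out are also still invited to assessments under {18b}, so fewer than half of the outcomes may be missing.

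Three further inferences go too far:

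- A rank test is not incompatible with an effect size and interval, since rank-based versions exist. The problem is that the plan does not say which it will report.
- The choice is conditioned on distributions, not on treatment results, and the simulation showed no material type I error inflation.
- No probability that some outcome is switched to a rank test can be given, because the protocol fixes neither the number nor the level of the normality checks, and outcomes in the same participants need not be independent.

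None of this answers the point about the test. The distribution-based rule is stated outright, so it is not a detail deferred to the SAP. A SAP naming a single test would contradict it.

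**Conclusion.** The point holds in two parts of different strength.

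The data-dependent choice of test is explicit. It leaves the primary estimand open, allows it to differ across the primary outcomes, and does not pool simply under multiple imputation.

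The absence of a specified baseline-adjusted analysis is a precision gain not secured, rather than a demonstrated loss. Adjustment gains power at either retained sample size, from a little over 2 percentage points at 52 per arm with r = 0.3 to 17 points at 40 per arm with r = 0.7. These sizes rest on an assumed r, on 0.64 being standardised on unadjusted scores and, for the smaller sample, on dropout meaning missing outcomes.

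The trial remains valid without the change. It should still be made, because it fixes the primary question in advance and uses data already being collected.

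**What to change.** In Statistical methods {20a}, delete the distribution-based choice of test. State one primary analysis that applies whatever distribution is observed: for each primary outcome, the 6-week score on arm and the same measure's baseline score (ANCOVA, or a mixed model covering 6 and 12 weeks). Fit it in each imputed data set and pool. Report the adjusted mean difference with its 95% confidence interval. Keep rank-based or bootstrap analyses as named sensitivity analyses, and align the sentence under Outcomes {12}.

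If the sample size section is to take credit for adjustment, state the assumed r and its source. Correct the dropout allowance separately; adjustment should not be used to cover it.

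The cost is protocol and SAP wording, settled before any unblinded outcome data are examined. No extra participants, visits or measurements are needed, and the planned software can fit the model.

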### Participant timeline {13}

**Table Tabb:** The following table explains the schedule of enrolment, intervention, and assessment

	Timeline for the study									
	Screening	Baseline	Week							Completion
Week			1	2	3	4	5	6	7	13
**Enrolment:** **Eligibility screening** **Informed consent** **Baseline assessments** **Allocation**										
	**X**									
	**X**									
		**X**								
		**X**								
**Intervention period in both arms**			**X**	**X**	**X**	**X**	**X**	**X**		
**Assessments** **Socio-demographic proforma** **BACS** **SOFS** **SSTICS** **MANSA** **RSES** **Semi structured Interview**		**X**								
		**X**							**X**	**X**
		**X**							**X**	**X**
		**X**							**X**	**X**
		**X**							**X**	**X**
		**X**							**X**	**X**
									**X**	

*BACS*, Brief Assessment of Cognition in Schizophrenia

*SOFS*, Socio-Occupational Functioning Scale

*SSTICS*, Subjective Scale to Investigate Cognition in Schizophrenia

*MANSA*, Manchester Short Assessment of Quality of Life

*RSES*, Rosenberg Self-Esteem Scale

### Sample size {14}

A Sample size of 104 participants (52 in each arm) is required based on the outcome indicators of cognitive performance with an effect size of 0.64 between the intervention and control groups, with 90% power and 5% alpha error using R 4.0.3 “pwr.t.test” software. A dropout rate of 50% has been assumed based on previous experiences and studies done using CCT. Therefore, the total number of recruited subjects at both sites will be 156 rounded up to 160 participants in total [22].

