### Trial design {8}

The proposed study will be a multicenter assessor-blinded randomized controlled trial conducted at two clinical sites in Chennai, India. It will be a parallel group study, with a 1:1 allocation ratio, evaluating superiority of V-CCT over an active control intervention. The intervention sessions for both the groups will be delivered virtually, and participants will join the sessions from home using a tablet/computer.

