### Plans to promote participant retention and complete follow-up {18b}

Both intervention and active control sessions will be delivered virtually for 6 weeks, consisting of two sessions per week. This schedule may potentially result in participant dropout due to various reasons. To ensure better retention rates and complete follow-up, the facilitators of both the intervention and active control groups will create an independent WhatsApp group for participants in each arm where all updates regarding the sessions will be posted.

Participants who drop out will still be invited to the end-line and follow-up assessments, unless they explicitly express disinterest. Flexible scheduling options will be provided for assessments and intervention sessions to accommodate participants’ availability based on the consensus of the group.

A subsample of participants who have dropped out of the intervention will be approached for a semi-structured interview to understand their experiences, barriers, and facilitators in attending the sessions virtually.

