### Methods in analysis to handle protocol non-adherence and any statistical methods to handle missing data {20c}

We will employ intention-to-treat (ITT) analysis to address protocol non-adherence, which helps preserve the randomization. To deal with any missing data points, we will employ multiple imputation techniques, which help with the retention of statistical power. We will also perform sensitivity analysis to assess the robustness our results hold up against alternative assumptions on missing data.

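### The stated 90% power belongs to 52 evaluable participants per arm at an undiluted 0.64, and does not describe the planned intention-to-treat comparison of 160 randomised participants

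*Protocol article*

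**What the plan says.** Sample size {14}: "A Sample size of 104 participants (52 in each arm) is required" for "an effect size of 0.64 between the intervention and control groups", "with 90% power and 5% alpha error". It continues: "A dropout rate of 50% has been assumed based on previous experiences and studies done using CCT". Recruitment is then set at 156 and rounded up to 160. Trial design {8} fixes equal arms ("with a 1:1 allocation ratio"), so 80 per arm are randomised. The section does not say whether 0.64 is an effect in people who attend or in everyone randomised, nor whether the 50% refers to leaving the sessions or to missing outcomes.

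The retention section {18b} speaks of dropout from a schedule of two sessions a week for six weeks, and adds: "Participants who drop out will still be invited to the end-line and follow-up assessments, unless they explicitly express disinterest".

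The statistical methods section {20a}: "The effectiveness of V-CCT will be evaluated using an intention-to-treat (ITT) analysis". Section {20c}: "We will employ intention-to-treat (ITT) analysis to address protocol non-adherence, which helps preserve the randomization". The same section plans multiple imputation for missing values, with sensitivity analyses.

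The Discussion names a higher risk of missing data as a limitation and gives the 160 recruits, at 50% dropout, as part of the response.

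**The concern.** One word does two jobs. In the sample size section, dropouts are people whose places must be refilled so that 104 remain, and those who remain carry the whole 0.64. In the retention and analysis sections, someone who stops attending is still invited to the outcome visit and still counts in the arm to which they were randomised. A participant cannot be both replaced in the power calculation and present in the comparison at full effect.

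With half the sample affected, this is not a rounding matter. Depending on which meaning holds and on what those who stop gain, the power of the primary comparison lies well below or well above the stated figure. A non-significant ITT result would be read against a 90% that was never computed for that analysis.

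**Working it through.** **Inputs.** From Sample size {14}: effect 0.64 (standardised, SD 1), alpha 5%, power 90%, 52 per arm, dropout 50%, 160 recruited. From Trial design {8}: 1:1 allocation, so 80 per arm. Sidedness is not stated; a two-sided two-sample t-test is used because it reproduces the plan's figure.

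**Step 1: reproduce the plan's figure.** At 0.64, two-sided 5% and 90% power, the normal approximation gives 52 per arm and the t-test gives 52.3. Power at 52 per arm is 89.8% (t-test). A one-sided test would need only 42 to 43 per arm. So 104 reproduces as a two-sided calculation with 0.64 applied in full to every evaluable participant.

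**Step 2: what the inflation allows for.** 104 × 1.5 = 156. The loss that leaves 104 is 1 − 104/156 = 33.3%, or 1 − 104/160 = 35% after rounding up. Keeping 104 after a 50% loss would need 104/(1 − 0.5) = 208.

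**Step 3: the 50% means lost outcomes.** 160 × 0.5 = 80 observed, or 40 per arm. Power at 0.64 with 40 per arm is 80.7%. This counts observed outcomes only.

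**Step 4: the 50% means stopped sessions, with everyone assessed.** Assume that 0.64 is the effect in attenders and that those who stop keep a share *f* of it. The documents give no value for *f*, so its whole range is shown.

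ITT effect = 0.64 × (0.5 + 0.5*f*), with 80 per arm:

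| *f* | ITT effect | Power |
|---|---|---|
| 0 | 0.32 | 52.1% |
| 0.25 | 0.40 | 71.0% |
| 0.50 | 0.48 | 85.5% |
| 0.75 | 0.56 | 94.1% |
| 1 | 0.64 | 98.0% |

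Allowing for the extra variance from mixing attenders and non-attenders in the V-CCT arm changes little: 50.1% at *f* = 0 and 85.0% at *f* = 0.5.

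The smallest effect with 90% power at 80 per arm is 0.516. Solving for *f*: (0.516/0.64 − 0.5)/0.5 = 0.61.

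**Step 5: would correcting the inflation formula settle it?** Not in every case. With 208 recruited and all assessed (104 per arm), *f* = 0 gives 63.2%. At *f* = 0, 90% power needs about 207 per arm.

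**Step 6: 0.64 is already an ITT effect.** Nothing is then diluted: 98.0% if all 80 per arm are assessed, and 80.7% if only 40 per arm are.

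**The case against.** Sizing a trial for evaluable participants, inflating for loss and then analysing by ITT with imputation is common practice. The Discussion supports reading the 50% as missing data. On that reading, inflating recruitment is the usual step and only the formula is at fault. The invitation to assessments is a retention effort, not a forecast that all 160 will be seen. These points stand, and they are why the case of lost outcomes (81%) has to be shown beside the dilution cases.

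A reader might infer that 0.64 is a completer effect and that the trial is therefore badly underpowered, at 52%. The documents do not support this. They do not say where 0.64 comes from beyond a citation. If it comes from trials with similar non-attendance analysed as randomised, the dilution is already in it. A share of zero would also mean that someone who leaves part-way through twelve modules gains nothing, which nothing in the protocol claims. The pilot described under Rationale of the study had 80% completing all sessions, though one-to-one rather than in groups. With 20% stopping, even *f* = 0 gives an effect of 0.512 and 89.6% power.

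A reader might also infer that the calculation allows for the full 50% dropping out. It does not: the multiplier of 1.5 covers about a third.

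The objection does not rescue the stated figure. Whichever meaning is chosen, 90% at 52 per arm is not the power of the ITT comparison of 160 randomised participants, and the reader cannot tell which meaning applies.

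**Conclusion.** The point holds as a mismatch between a stated power and the planned analysis, not as proof that power is lost. Power is about 81% if the 50% are lost to assessment. If all are assessed and 0.64 is the attender effect, it runs from 52% to 98% and reaches 90% only when those who stop keep about 61% or more of the benefit. If 0.64 is an ITT effect and all are assessed, it is 98%.

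The direction is therefore open. It turns on three things that the protocol leaves unstated: what dropout means, how many of those who stop are assessed, and what kind of effect 0.64 is. The figures assume a two-sided 5% t-test with equal arms and no gain in precision from imputation or covariates. The correction is worth making, because a reader will judge the result against the stated 90%.

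**What to change.** In Sample size {14}:

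- Distinguish stopping the sessions (outcome still collected, participant kept in the ITT analysis) from a missing week-6 outcome, and give an assumed rate for each.
- State whether 0.64 is an ITT effect or an effect in attenders, and its source.
- Allow for missing outcomes by dividing by one minus the loss, and for non-attendance by a stated dilution of the effect.
- Restate the power of the 160 randomised for the ITT comparison over the whole range. For example: about 81% if half have no week-6 outcome; if all are assessed and 0.64 is the attender effect, 52%, 71%, 85%, 94% or 98% when those who stop keep 0%, 25%, 50%, 75% or 100% of it; 98% if all are assessed and 0.64 is already an ITT effect.

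Use the same definition of dropout in the retention section and the Discussion. Keep ITT as the primary analysis. A complier-average estimate from the attendance in the session logs is optional, and the correction does not depend on it.

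The cost is the rewording of one paragraph. No extra participants or data are needed, but the stated power may become less favourable.

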### Rationale of the study

Compensatory cognitive training (CCT) was developed to be “brief, practical, low-tech, engaging to clients, and portable enough to be delivered in the community” [9]. It teaches strategies to help clients work around their deficits, linking strategies to goals and roles in the community [10]. A meta-analysis on CCT identified 26 studies across 7 countries and reported a medium effect on functioning and relative durability of effects on cognition [11]. As there are no structured cognitive intervention modules in India, we have adapted the English CCT manual for use in an urban population in Chennai, India. Our study found CCT to be feasible in face-to-face group sessions in our setting [12].

Virtual psychological interventions have been tested and used before and during the pandemic [13–16]. The National Mental Health Survey 2016 also recommends the use of technology to improve services. The SCARF team has piloted virtual one-on-one CCT (V-CCT) and found it to be feasible and acceptable as a virtual intervention. This was delivered using the culturally adapted English version of CCT. According to the unpublished data, 80% of the participants completed all 12 sessions of V-CCT. Pre-post differences were observed in specific domains of cognition. The participants reported benefits such as reduced travel time and cost and made them feel independent as they did not have to rely on their caregivers to attend sessions.

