## Discussion

This study aims to evaluate the effectiveness of compensatory cognitive training (CCT) in improving cognitive deficits among persons with schizophrenia, compared to an active control intervention. The CCT Intervention will be delivered through virtual platforms in a group format. The study also employs an active control intervention, manualized and translated into Tamil, comprising various fun and befriending activities. The active control intervention helps control for the experience of a group intervention online from home with a facilitator. In addition to assessing improvements in cognition and functioning, the study intends to assess if cognitive interventions can bring a change in quality of life and self-esteem. One of the key strengths of this study is its randomized controlled trial (RCT) design, which effectively controls for baseline confounding factors. Furthermore, it utilizes a superiority study design to test whether the V-CCT intervention out forms the active control arm in improving cognition. While the use of manualized interventions enhances standardization and replicability, there are several limitations to consider. These include digital literacy challenges, and a higher risk of missing data, given the population of persons with lived experience of schizophrenia. In order to address these concerns, we plan to recruit 160 participants, assuming the 50% drop out rate.

We will employ a comprehensive approach to enhance reliability and validity of our study, by including ITT for protocol non-adherence, multiple imputation for missing data, and sensitivity analysis to check robustness of our findings.

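### The 50% dropout allowance multiplies 104 by 1.5 instead of dividing by 0.5, so if half the outcomes are lost, 160 recruits give about 81% power, not 90%

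*Protocol article*

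**What the plan says.** Sample size {14} of the protocol article first gives the number to be analysed: "A Sample size of 104 participants (52 in each arm) is required". This is "with an effect size of 0.64 between the intervention and control groups" and "with 90% power and 5% alpha error using R 4.0.3", from the R routine for a two-sample t-test. Trial design {8} confirms equal allocation. The section then allows for attrition: "A dropout rate of 50% has been assumed based on previous experiences and studies done using CCT". The recruitment target follows directly as a consequence: "Therefore, the total number of recruited subjects at both sites will be 156 rounded up to 160 participants in total".

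The Discussion names missing data as a limitation and answers it with the same pair of figures: "we plan to recruit 160 participants, assuming the 50% drop out rate".

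Two other sections bear on what a dropout costs. The retention section {18b} says that people who drop out are still asked to attend the later assessments unless they decline. The section on non-adherence and missing data {20c} plans an intention-to-treat analysis with multiple imputation. Neither is used to justify the factor applied to 104.

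**The concern.** An allowance for dropout should return the evaluable number once the assumed loss has occurred. The recruited number times the retained fraction should therefore equal 104. Here 156 × 0.5 = 78 and 160 × 0.5 = 80, both well short. The target looks like the common slip of adding the dropout percentage to the required number instead of dividing by the fraction retained. At small dropout rates the two differ little; at 50% they differ by a third of the original requirement or more.

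What is at stake is how the result will be read. The sample size section tells readers that the trial has 90% power after a 50% loss. If a loss of that size reached the primary outcome and the trial were null, readers would credit it with more sensitivity than it had.

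**Working it through.** **Inputs**, all from Sample size {14} except the allocation ratio, which is in Trial design {8}: effect size d = 0.64 (SD = 1); power 90%; alpha 5%; 1:1 allocation; 104 evaluable; 50% dropout; 156 rounded to 160 recruited. The section does not say whether the test is one- or two-sided.

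**Step 1: reproduce the 104.**
- Normal approximation: n per arm = 2(1.960 + 1.282)² / 0.64² = 51.3, rounded up to 52.
- Noncentral t, two-sided: 52.3 per arm.
- Noncentral t, one-sided: 42.5 per arm, which does not match.

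The plan's 52 per arm is therefore a two-sided calculation and is right to within rounding. Power at exactly 52 per arm is 89.8% by the t-test (90.4% by the normal approximation).

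**Step 2: reproduce the 156.**
- 104 × (1 + 0.5) = 156, an exact match.
- 104 / (1 − 0.5) = 208, the number that leaves 104 after half are lost.
- Gap between 208 and the planned 160: 48 participants.

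**Step 3: the loss that the planned numbers can absorb.**
- From 156: 1 − 104/156 = 33.3%.
- From 160: 1 − 104/160 = 35%.

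**Step 4: power if 50% have no week-6 outcome** (two-sided 5%, d = 0.64).

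| Recruited | Evaluable | Per arm | Power, t-test | Power, normal |
|---|---|---|---|---|
| 208 | 104 | 52 | 89.8% | 90.4% |
| 160 | 80 | 40 | 80.7% | 81.7% |
| 156 | 78 | 39 | 79.7% | 80.7% |

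With 160 recruited, the chance of missing the assumed effect goes from 10.2% (100 − 89.8) to 19.3% (100 − 80.7). The effect detectable with 90% power at 40 per arm is 0.734, against the planned 0.64.

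**Step 5: if dropout means leaving the sessions.** With 160 recruited and 80 leaving, 104 assessed participants need 104 − 80 = 24 of the leavers (24/80 = 30%) to attend week 6. If half of them attend, 80 + 40 = 120 are assessed (60 per arm), and power at d = 0.64 is about 94%. That is before any dilution of the effect because these people stopped the sessions.

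**The case against.** The strongest reply is that dropout need not mean a missing outcome. The retention section speaks of people leaving the intervention and still invites them to the end-line assessment, and the analysis is by intention to treat with multiple imputation. Step 5 shows that modest attendance by leavers would bring the assessed number back to 104.

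This part stands: 81% is a conditional figure. A reader might infer that the trial will have 81% power. The documents do not support that, because they do not say what share of dropouts will lack the week-6 outcome.

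The reply does not rescue the calculation. The sample size section treats the 50% as a loss to be made good by recruiting more, and the Discussion links it to missing data. If the 50% meant session attendance only, a factor of 1.5 would still not follow from it. Nor does imputation by itself restore outcome information that was never collected.

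A reader might also be tempted to set the 50% against the feasibility work in the Rationale, where "80% of the participants completed all 12 sessions of V-CCT", and conclude that the dropout assumption is too pessimistic or that 35% is safe. The documents do not support this. That work was one-on-one, used the English version and counted completed sessions. The trial is an online group intervention for Tamil speakers, and what matters for power is outcome retention. The 50% is attributed to other experience and studies that are not shown.

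Finally, the Discussion should not be read as claiming 90% power at 50% dropout. It repeats only the pairing of 160 with 50%; the 90% appears in the sample size section alone.

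**Conclusion.** The inflation is wrong as written. The base requirement of 104 reproduces, but the step from 104 to 156 multiplies by 1.5 where a 50% loss calls for division by 0.5. Under the plan's own inputs, 160 recruits fall 48 short of the 208 needed. If all the assumed dropouts lack the primary outcome, power is about 81% instead of 90%.

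The power figures rest on a two-sided t-test (the only reading that gives 52 per arm), equal loss in the two arms, d = 0.64 and analysis of observed outcomes. They would be better than 81% to the extent that people who leave the sessions still attend week 6. The inconsistency between power, dropout and recruitment does not depend on that. Whether 50% is itself a good assumption cannot be judged from the documents and is not part of the point. Power of about 81% does not make the trial unviable; it is simply not the power stated.

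**What to change.** Keep 160 and correct the statement in Sample size {14}, for example:

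> With 160 recruited and 50% lost to the primary outcome at 6 weeks, 80 participants (40 per arm) are evaluable, giving about 81% power for an effect size of 0.64 (two-sided 5%). About 90% power holds only if loss to the outcome is at most 35%. The 81% assumes that every participant who drops out lacks the outcome; power is higher if some of them attend the assessment.

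Align the Discussion, so that 160 is no longer presented there as the answer to a 50% dropout without this qualification. Do not use the session completion in the feasibility work to argue for a lower dropout rate.

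The cost is wording only: no extra participants and no change to design, outcomes or analysis. The downside is that the stated power becomes less favourable. Keeping both 90% power and full loss of half the outcomes would instead take 208 recruits, 48 more than planned.
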